### Design

This noninferiority, prospective, randomised, controlled, single-blind, two-group study will be conducted in the emergency subunits of the Nantes University Hospital. Eligible patients with irreversible pulpitis in the first or second mandibular molars requiring emergency dental care will be included in the study. Diagnosis will be based on clinical and radiographic examination. Two parallel groups will be randomised at a ratio of 1:1 so that patients will either receive (1) intraosseous anaesthesia or (2) inferior alveolar nerve block anaesthesia. This manuscript used the SPIRIT reporting guidelines [30].

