### Outcomes

The main outcome of this study is to compare the time required in minutes for the cardiovascular parameters to return to their initial values between the two techniques: ICA with the QuickSleeper™ system versus the reference technique: inferior alveolar nerve block (IANB). The timing of the evolution of the parameters is based on 3 phases: “baseline” from T0 to T+4 minutes, “anaesthesia” from T+4 to T+8 minutes, and “pulpotomy” from T+8 to T+14 minutes. The return to baseline values will be defined as a success if 3 successive values of heart rate and blood pressure (systolic and diastolic) are identical to those recorded before injection. On the other hand, if there is an absence of 3 successive values of these two parameters, it is defined as a failure.

Secondary outcomes include:The O^2^ measurement performed during the 3 phasesThe efficacy of the anaesthesia with a VAS (visual analogue scale) of 0 and that the pulpotomy was completed successfully: the patient is asked about his or her perception of pain before the operation at D0 and D+1, D+2, and D+3Post-operative careInvestigation of factors associated with delay in recovery of cardiovascular parameters (heart rate, dental anxiety, age, gender, and use of analgesics in the 6 h before surgery)

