### Determination of sample size

The sample size calculation was based on the noninferiority hypothesis in a pilot study that there will be an expected mean difference of 1 min 30 s between the two anaesthetic techniques with regard to the time taken for the values to return to the initial ones. According to the reported results from the few studies available, the proportion of patients having successful anaesthesia and better pain control in the reference group (intraosseous anaesthesia) would be 93%. The noninferiority margin was defined as 20%. The significance was set at 1.7% for the 3 main criteria (heart rate, systolic and diastolic blood pressure) and 5% for the secondary criteria. Thus, using a bilateral test with an epiR package 0.98-87 (Biostatgv), 72 patients (36 patients per arm) will be included in the study.

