### Statistical analysis

The analysis will be based on intention-to-treat (ITT) using the “missing=failure” strategy. A robustness analysis, supported by the per-protocol approach, will be carried out if the patients present with protocol deviations (error of randomisation). Qualitative variables will be described by the percentages and numbers of each modality. Quantitative variables will be described by means and standard deviations. Confidence intervals at 95% will be presented.

A paper case report form (CRF) will be created for each patient inclusion for data collection and will be based on the establishment of a clinical database. All information required by the protocol must be provided in the CRF, necessary for statistical analyses.

To assess the primary endpoint (time to return to baseline heart rate and blood pressure), the mean values will be estimated by the Kaplan-Meier method (survival curves) and compared using Log-Rank tests. To assess the secondary endpoint (time to baseline O_2_ and change in measurements over time), the 2 arms will be compared in the same way as the heart rate and blood pressure parameters. Univariate and multivariate Cox models will be used to investigate the factors associated with the time to the baseline of cardiopulmonary constants. The difference in pain between D0 and D+3 will be compared between the 2 groups a Student’s *t*-test or a Wilcoxon test. Data for the analysis are collected from the first questionnaire (French version of Corah’s dental anxiety scale), the three phases of cardiopulmonary monitoring, the VAS assessment, and the postoperative questionnaire given to the patient at the end of the procedure. The information recorded on the postoperative questionnaire will be collected by a telephone call 3 days after the procedure. All the data collected will be typed and inserted into an Excel spreadsheet for data entry in a secure computer network of Nantes University Hospital. The investigative team, mainly the investigators as well as the study technicians involved in this study protocol will have access to the data collected.

In regard to the post-trial care, the patients will either continue their dental care with their appointed dentist, or in the case where they do not have one, they will be following appointments at the Nantes University Hospital.

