Furthermore, this technique has considerable expected benefits (patient comfort, rapidity of action, reproducibility). In addition, there is less risk of technical failures, such as a blocked or broken needle and the ability to retrieve the needle. The QuickSleeper™ system is also able to administer the anaesthetic solution at varying speeds, in the context of a para-apical or an intraligamentary injection with the same device regardless of the location, density, and resiliency of the soft tissues at the injection site.

Adverse effects of intraosseous anaesthesia are associated with an elevated heart rate (tachycardia, malaise). The main causes of an elevated heart rate are related to the patient's perception, fear, and anxiety, exacerbated by the symptoms of irreversible pulpitis or by the amount of vasoconstrictor used. Because this elevation is transient, it does not pose a serious cardiovascular risk, rendering its effect negligible. In patients whose medical condition suggests caution in administering epinephrine, mepivacaine may be an acceptable alternative [24]. The main objective of this trial will be to conclude that the time required for the cardiorespiratory parameters to return their initial values will be similar to the two anaesthetic techniques used. This study should provide better data about potential risk with ICA technique such as the QuickSleeper™ system in healthy or cardiovascular-risk patients.

This new approach in dentistry would increase the number of successful pulpal anaesthesia in emergency endodontic treatments by avoiding IANB failures and alleviating compliance of patients.

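### The trial is declared noninferiority on time to return to baseline, but its stated primary analysis is a log-rank difference test with no noninferiority decision rule and no clear margin on the time scale

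*Protocol article*

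**What the plan says.** The Design section calls the trial "This noninferiority, prospective, randomised, controlled, single-blind, two-group study". The Outcomes section sets the main outcome as a comparison of times, to "compare the time required in minutes for the cardiovascular parameters to return to their initial values between the two techniques". The Discussion says the main objective is to conclude that "the time required for the cardiorespiratory parameters to return their initial values will be similar to the two anaesthetic techniques used".

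For the primary endpoint, the Statistical analysis section says that "the mean values will be estimated by the Kaplan-Meier method (survival curves) and compared using Log-Rank tests". It adds that 95% confidence intervals will be presented, but ties them to no margin.

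The Determination of sample size section gives three ingredients:
- Its noninferiority hypothesis is linked to an expected mean difference of 1 min 30 s in return time.
- It then states that "the proportion of patients having successful anaesthesia and better pain control in the reference group (intraosseous anaesthesia) would be 93" per cent, and directly afterwards "The noninferiority margin was defined as 20" per cent.
- Significance is 1.7% for each of three main criteria (heart rate, systolic and diastolic pressure), with a two-sided test and 72 patients, 36 per arm.

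The two sections disagree on the comparator. The sample size section labels intraosseous anaesthesia the reference group, while Outcomes has ICA "versus the reference technique: inferior alveolar nerve block (IANB").

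**The concern.** The null hypothesis of a log-rank test is that the two curves are equal. Failing to reject it does not show that one technique is no worse than the other by more than a tolerable amount. That needs a margin and a confidence limit to compare with it, and the stated primary analysis has neither.

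A plan whose aim is to conclude similarity, and whose only test is a difference test, invites the inference from a non-significant p-value to similarity. That inference becomes easier as the trial gets smaller or noisier. It also becomes easier as alpha is split: the 1.7% level protects against false claims of difference, but here it makes non-significance more common. The claim at stake is the cardiovascular safety of the intraosseous technique.

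The Kaplan-Meier mean is a second difficulty. Monitoring stops at T+14 and the article expects some patients not to return to baseline. If the curve has not reached zero by then, the unrestricted mean cannot be estimated. A log-rank test does not compare means in any case.

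**Working it through.** **1. What 72 corresponds to.** The article does not state power or SD, so these are varied.

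- *Success proportion, 93% in both arms, margin 20 points.* Per arm n = 2 × 0.93 × 0.07 × (zα + zβ)² / 0.20². Two-sided 5% with 90% power: 0.1302 × (1.960 + 1.282)² / 0.04 = 34.2, so 35 per arm and 70 in total. One-sided 5% with 95% power: 36 per arm, 72 in total. Two-sided 1.7% (z = 2.387) at 80%, 85% and 90% power: 68, 78 and 88 in total; the first becomes 72 only with an unstated 5% dropout.
- *Time, difference 1.5 min, two-sided 1.7%.* The SD implied by 36 per arm is 1.5 / [(2.387 + zβ) × √(2/36)], which is 1.97 min at 80% power and 1.74 min at 90%. No SD is given, so 72 cannot be rebuilt on this endpoint.

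The 20% margin and the 72 therefore fit a noninferiority calculation on anaesthetic success more readily than a log-rank test on time at 1.7%. This is supporting evidence only.

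**2. How often a single log-rank test is non-significant when one arm is 1.5 min slower.** Schoenfeld: power = Φ(|ln HR| × √events / 2 − 2.387), taking all 72 patients to return. With exponential times, HR is the ratio of the means.

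| Means (min) | HR | Power | Non-significant |
|---|---|---|---|
| 3 vs 4.5 | 0.667 | Φ(1.720 − 2.387) = 25% | 75% |
| 4 vs 5.5 | 0.727 | 15% | 85% |
| 5 vs 6.5 | 0.769 | 10% | 90% |

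Simulation with 36 per arm and censoring 10 min after T+4 gives 77%, 86% and 91% non-significant. At two-sided 5% the first row would be about 60%.

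Exponential times force the SD to equal the mean. With less dispersed gamma times and means of 3 and 4.5 min, simulated power is about 50%, 68% and 83% for shapes 2, 3 and 4, so non-significance is 50%, 32% and 17%. For means of 5 and 6.5 min, non-significance runs from about 90% (exponential) to 60% (shape 4). Overall the range is about 20% to 90%.

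These figures are per criterion. If all three have the 75% figure, the chance that none is significant is 0.75³ = 42% under independence and 75% under perfect correlation.

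**3. Whether 1.5 min could simply become the margin.** A restricted mean over the 10 min from T+4 to T+14 is m × (1 − e^(−10/m)) for exponential times:
- 3 vs 4.5 min: 4.01 − 2.89 = 1.12 min
- 4 vs 5.5 min: 4.61 − 3.67 = 0.94 min
- 5 vs 6.5 min: 5.10 − 4.32 = 0.78 min

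A true delay of exactly 1.5 min would lie well inside a 1.5 min margin on that scale. Carrying the figure over would favour a noninferiority claim.

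**4. What 72 patients could support.** On an untruncated mean with a 1.5 min margin, true difference 0 and two-sided 1.7%, total N at 80% / 90% power is 76 / 96 for SD 2, 116 / 150 for SD 2.5 and 168 / 216 for SD 3. On the hazard-ratio scale, 72 events exclude a margin of exp(−2 × (2.387 + 0.842) / √72) = 0.47 with 80% power.

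**The case against.** A reader might infer that this trial can never show noninferiority. That goes too far: a log-rank result significantly favouring ICA would imply it, although that is a superiority finding and not the conclusion the Discussion seeks.

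A reader might also infer that no time figure enters the noninferiority reasoning. The sample size section does open by linking that hypothesis to 1 min 30 s. The wording is ambiguous, but it calls the figure an expected difference, so it cannot be taken as a margin. Nor can 20% be taken as a relative margin on time, since nothing applies it to time.

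The planned 95% intervals could be compared with a margin, and the statistical analysis plan, which is not shown, might contain such a rule. That is fair, and it is why the point is not that detail is missing. The article itself fixes the hypothesis type, the margin, the alpha and the test, and they do not fit together. An analysis plan that follows the article inherits the mismatch; one that repairs it departs from the published text.

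The strongest objection is to the size. A flat 75% risk of a false finding of similarity is tempting, but it rests on exponential times and one control mean. The need for three successive matching values may well make times less dispersed than exponential. The 1 min 30 s also has no stated direction, so ICA being the slower arm is an assumption. This stands, and only the range is supportable.

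**Conclusion.** The mismatch holds with high confidence and rests on the text alone: a noninferiority aim on time, a difference test as the primary comparison, no decision rule, and a margin placed after a different endpoint. A non-significant log-rank test would not support the intended conclusion.

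The size is less certain. For one criterion at two-sided 1.7%, 36 per arm and a true 1.5 min delay in one arm, non-significance has a probability of about 20% to 90%, depending on the assumed distribution and control mean. The documents do not support a single figure, the claim that noninferiority is unattainable, or the use of 1.5 min as an established margin. Failure to rebuild 72 exactly does not decide the point. It needs correcting before the primary result is interpreted.

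**What to change.** Before database lock and any comparative analysis:

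- Replace the log-rank test as the primary decision with a confidence-limit rule for a between-arm effect measure. Examples are the difference in restricted mean time from start of injection to T+14, or a hazard ratio for return to baseline.
- Set and justify the margin on that same scale, allowing for truncation at T+14. Do not carry over the untruncated 1.5 min.
- Use interval limits that match the 1.7% level (a two-sided 98.3% interval) in place of the 95% intervals now planned.
- State whether all three criteria must meet the margin.
- Reconcile which technique is the reference between Outcomes and Determination of sample size, so that the direction of the comparison is fixed.
- Keep the Kaplan-Meier curves and log-rank test as descriptive support, drop the unrestricted Kaplan-Meier mean, and state that a non-significant log-rank test is not evidence of noninferiority.

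Patient blinding gives little protection here, because investigators randomise, treat and have access to the data. If comparative data have already been seen, label the margin post hoc and make no noninferiority claim.

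The cost is analysis-plan wording and a margin decision. Non-significance no longer counts as success, and 72 patients may give low power: with a 1.5 min margin on an untruncated mean, 80% power needs an SD of about 2 min or less. With inclusion due to end on 1 July 2022, that limitation should be stated and not met by enrolling more patients.

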### Interventions

The patient will be blinded to the affected group and will fill out the first questionnaire which is the French version of Corah’s dental anxiety scale [31] to assess his or her anxiety about dental care. Then, the patient will be placed with a cuff on the arm, and a pulse oximeter on the other finger connected to a blood pressure monitor to monitor the cardiovascular parameters (heart rate, systolic and diastolic blood pressure, and oxygen saturation) throughout the intervention.

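### The primary arm comparison is an unadjusted log-rank test although anxiety and heart rate, both listed as candidate factors for recovery time, are measured before injection: a valid test that may give up efficiency

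*Protocol article*

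**What the plan says.** For the primary endpoint, the Statistical analysis section plans Kaplan-Meier estimates of the time to return in each arm, to be "compared using Log-Rank tests". It names no covariates or strata for this comparison, and the Randomisation section names no stratification factor.

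The same section adds that "Univariate and multivariate Cox models will be used to investigate the factors associated with the time to the baseline of cardiopulmonary constants". Outcomes places this work among the secondary outcomes and lists the factors as "heart rate, dental anxiety, age, gender, and use of analgesics in the 6 h before surgery".

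Two of these factors are available before treatment in both arms:

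- **Anxiety.** Under Interventions, each patient completes a "dental anxiety scale [31] to assess his or her anxiety about dental care".
- **Heart rate.** Under Outcomes, the baseline phase runs "from T0 to T+4 minutes", before the anaesthesia phase. Heart rate and blood pressure are monitored from then on.

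The Discussion attributes a raised heart rate mainly to the patient's "perception, fear, and anxiety, exacerbated by the symptoms of irreversible pulpitis or by the amount of vasoconstrictor used".

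**The concern.** The article points to anxiety and heart rate as possible influences on recovery time and collects both before injection, but uses neither in the test that compares the arms. With 36 patients per arm and no stratification described, the arms may well differ somewhat on either factor by chance. If the factor is prognostic, that difference becomes noise in the arm comparison.

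What is at stake is precision and power in a small trial that tests three criteria at 1.7% each. The covariates are already being collected, so using them requires no new data.

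**Working it through.** The plan has no figure of its own on this point, and nothing in it gives the prognostic strength of anxiety or heart rate. The results below are therefore a range over stated assumptions.

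**Inputs from the article.** 36 per arm and 1.7% two-sided per criterion (Determination of sample size). Anaesthesia starts at T+4 and monitoring ends at T+14 (Outcomes), which leaves 14 − 4 = 10 minutes to observe a return.

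**Assumed.** Exponential times with a median of about 4 minutes; standardised normal covariates; log hazard of return changing by 0, 0.3, 0.5 or 0.7 per SD.

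**Step 1: chance imbalance.** The SD of the between-arm difference in a standardised covariate is √(2/36) = 0.236. So P(|difference| > 0.25 SD) = 29%, P(> 0.30 SD) = 20% and P(> 0.50 SD) = 3.4%.

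**Step 2: restricted mean time.** Each patient contributes min(time to return, 10 minutes). The arm difference was estimated with and without one covariate in simulated trials of 36 per arm (6,000 trials; repeated with 8,000 per setting). Equivalent patients per arm = 36 / variance ratio.

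| Log hazard per SD (assumed) | Variance ratio, adjusted/unadjusted | Repeat run | Equivalent per arm (from column 2) |
|---|---|---|---|
| 0 | 1.01 | 1.02 | about 36 |
| 0.3 | 0.953 | 0.95 | 36/0.953 = 37.8 (about +2) |
| 0.5 | 0.847 | 0.87 | 36/0.847 = 42.5 (about +6) |
| 0.7 | 0.764 | 0.77 | 36/0.764 = 47.1 (about +11) |

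Both estimators centre on the same difference in minutes. For irrelevant covariates, theory gives a variance inflation of about 1 + p/(72 − 3 − p). That is 1 + 1/68 = 1.015 for one covariate and 1 + 2/67 = 1.030 for two.

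**Step 3: what an imbalance does.** In the same simulations, a 0.30 SD imbalance moved the unadjusted difference by about 0.27, 0.41 or 0.54 minutes at log hazards 0.3, 0.5 and 0.7. Against the 1.5-minute expected difference in the sample-size section, that is 0.27/1.5 = 18%, 0.41/1.5 = 27% and 0.54/1.5 = 36%.

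**Step 4: the Cox route.** This used 1,500 trials per setting, three independent covariates of equal strength and a true conditional hazard ratio of 2.14. That is the ratio a log-rank test detects with 80% power at 1.7% if all 72 patients have an event: exp[(2.387 + 0.842)/√(72/4)] = 2.14.

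| Hazard ratio per SD, each covariate | Log-rank power | Adjusted Cox power | Log HR (SE), unadjusted | Log HR (SE), adjusted |
|---|---|---|---|---|
| 1.00 | 70% | 68% | 0.775 (0.272) | 0.808 (0.283) |
| 1.22 | 64% | 69% | 0.734 (0.272) | 0.812 (0.285) |
| 1.49 | 46% | 65% | 0.619 (0.275) | 0.797 (0.291) |
| 1.82 | 32% | 62% | 0.536 (0.279) | 0.802 (0.299) |

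The standard error rises slightly with adjustment. The power gain, from −1 to +30 points on unrounded figures, arises because the conditional log hazard ratio is larger than the marginal one. With no arm effect, rejection rates were 1.6% to 2.3% for the log-rank test and 1.9% to 2.3% for adjusted Cox, against a nominal 1.7%.

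**The case against.** The strongest reply is that nothing here is an error. A log-rank test is valid under 1:1 randomisation, its error rate already allows for chance imbalance, and Step 4 shows no better error control from adjustment. This stands. A reader might infer that the primary result would be biased or invalid, and the article does not support that.

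A reader might also infer that the trial names blood pressure as a driver of its outcome. It does not. Blood pressure is one of the three criteria and is absent from the factor list. Heart rate is listed only for investigation and without the word baseline, and the Discussion links anxiety to raised heart rate, not to time to return. Return is also defined against the patient's own pre-injection values, so anxiety may raise the target as well as the response. Its prognostic strength is therefore unknown.

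Nor can one conclude that the planned Cox models leave out the arm. The Abstract and Objectives describe the factor analysis as a matter between the two techniques, so including arm is a natural reading. Even then it remains a secondary investigation of factors, and the text does not make it the basis of the primary comparison.

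Two further limits stand. The gain is not free in every form: the variance reductions apply to the restricted-mean difference, whereas Cox adjustment changes the quantity estimated. And the Statistical analysis section describes no interval for time compared with a margin, so no stated non-inferiority decision currently turns on interval width.

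The argument that covariates belong in an analysis plan not shown here carries less weight. The article does more than stay silent: it names the primary test.

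**Conclusion.** The point holds as a missed efficiency. The primary comparison is fixed as an unadjusted log-rank test while two pre-injection measurements that the article itself lists as candidate factors go unused in it.

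The variance reduction for a difference in restricted mean time is roughly 5% to 24% if one covariate carries a log hazard of 0.3 to 0.7 per SD. If it carries nothing, the cost is 1% to 2%, or about 3% with two irrelevant covariates. These figures rest on exponential times, a 4-minute median and a 10-minute horizon; only the horizon follows from the article. The imbalance probabilities need only the 36 per arm and a normal approximation.

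This is a worthwhile, inexpensive improvement, not the correction of a mistake, and it would not settle how non-inferiority is to be tested.

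**What to change.** For each of the three criteria, pre-specify a covariate-adjusted estimate of the arm difference in restricted mean time to return, in minutes. The model would include arm, anxiety score and pre-injection heart rate (or the pre-injection value of the parameter concerned). Report the confidence interval at the 1.7% level, that is 98.3%, and keep the unadjusted log-rank result as a sensitivity analysis. Minutes match the scale of the main outcome and of the 1 min 30 s in the sample-size section.

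If a Cox model is used instead, state that it targets a conditional hazard ratio and that its benefit is power and not a smaller standard error.

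The cost is a sentence or two in the plan, fixed before the data are examined, with no new data collection. The downside is the slight loss of precision if the covariates prove not to be prognostic.

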Intra-osseous computerised anaesthesia (ICA), such as the QuickSleeper™ system (Dental Hi-Tec, Cholet, France), administers the solution with a computerised control into the diploë (a richly vascularized bone) at a local rate and pressure. Thus, the QuickSleeper™ system is a form of ID in which the anaesthetic is delivered close to the root apices and associated periradicular tissues, leading to a greater reduction in periradicular sensation. The anaesthesia takes effect more rapidly since the solution is deposited close to the apex of the tooth at an axis of 15° to 30°. Thus, this form of delivery increases its effectiveness and reduces the risk of tissue necrosis, with better pain control (42 to 93% according to studies) [22, 23]. No soft tissue numbness occurs, and relatively fewer amounts of anaesthetic solution are needed. However, due to the fast diffusion of the anaesthetic solution in the diploe, the heart rate accelerates via the added effect of vasoconstrictors. This elevation is transient, and its effect is negligible and does not pose serious cardiovascular risk [12, 22].

There are currently many clinical studies that have evaluated cardiac parameters during IO administration. The heart rate increases in a reversible manner depending on the speed of injection [12]. The Stabident™ system showed a significant increase in heart rate of 8-28 beats/minute (BPM) on average with 2% lidocaine 1:100,000 epinephrine according to 3 authors [24–26]. By comparison, the X-Tip injection elevated the heart rate by 9–10 beats per min [27]. In regard to other parameters such as oxygen saturation and blood pressure, Pereira et al found no differences in either of them when using the X-Tip™ system but noted a significant increase in heart rate with 4% articaine (1:100,000 or 1:200,000 epinephrine) for anaesthetizing irreversible pulpitis lower molars [23]. Therefore, the accelerated heart rate could be a potential adverse effect of this injection [27].

Articaine is a common anaesthetic agent and a member of the amide family. The presence of its thiophene group increases its liposolubility, facilitating its diffusion into both nerve sheaths (such as the inferior alveolar nerve) and neural membranes of individual axons comprising a nerve trunk. The lower pKa of articaine would translate into a greater percentage of the drug in the active base form and its plasma protein binding is 95% higher than most other local anaesthetics [25–27].

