### Adverse events

Considering the low risks and constraints of this study, no adverse event related to the trial is expected. In addition to the measurements of blood pressure and heart rate variations, which are the objectives of the present protocol, the suspected AEs related to the administration technique or anaesthesia will be traced in the CRF and analysed according to the study schedule by internal monitoring. They will not be notified to the sponsor, even if they are serious. Any adverse event is linked to a failure of anaesthesia.

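### The stated log-rank comparison fits time to baseline O2 but not the other half of the same secondary endpoint, change in measurements over time

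*Protocol article*

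**What the plan says.** In the protocol article, Statistical analysis, the primary endpoint (time for heart rate and blood pressure to return to baseline) is to be "estimated by the Kaplan-Meier method (survival curves) and compared using Log-Rank tests". The next sentence takes up the secondary endpoint, described as "time to baseline O_2_ and change in measurements over time", and states that "the 2 arms will be compared in the same way as the heart rate and blood pressure parameters".

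The Outcomes section gives the measurement frame: "The timing of the evolution of the parameters is based on 3 phases", with baseline from T0 to T+4 minutes, anaesthesia from T+4 to T+8 and pulpotomy from T+8 to T+14. It lists oxygen as a measurement taken during all three phases. It defines return to baseline, for heart rate and blood pressure, as three successive values equal to those before injection. Determination of sample size sets the significance level at 1.7% for the three main criteria and "5% for the secondary criteria".

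**The concern.** Two different kinds of quantity share one method. Time to baseline O2 is a duration, with one value per patient, possibly censored. Change over time is a series of readings per patient. A method built for the first is assigned to both.

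At stake is what the result can be taken to mean. A null log-rank result filed under change over time could be reported as showing that the two techniques moved the readings alike. It would show only that no difference was found in when the readings came back. Two techniques with similar recovery times but different depths of change would look the same on the only between-arm test attached to this endpoint.

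**Working it through.** There is no stated figure to reproduce. The check sets the methods named in Statistical analysis against the quantities they are meant to compare.

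**1. What the cross-reference points to.** For heart rate and blood pressure, the section gives Kaplan-Meier curves and log-rank tests and no other between-arm comparison.

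**2. What log-rank uses.** For each patient it needs an event or censoring time, an event indicator and the arm. At each event time it sums observed minus expected events in one arm. The readings enter only through the event time they produce. If a patient's readings are altered in a way that leaves that time and indicator unchanged, the statistic does not move.

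**3. Fit to each part.**
- Time to baseline O2: it fits, assuming the rule of three successive values is carried over to oxygen.
- Change over time: no event is defined. The only event rule in the article concerns return to baseline, which is the first part again.

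**4. Other methods in the section.**
- The Cox models address factors associated with time to baseline, which is again a duration.
- The Student's t-test or Wilcoxon test is assigned to the pain difference between D0 and D+3.
- Means, standard deviations and 95% intervals are descriptive. They may show a difference in readings but are not assigned as the comparison.

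**5. What a comparison of readings could deliver.** Inputs from the document: 36 patients per arm and the 5% secondary level. Assumptions: a two-sided test, every patient contributing readings, and a comparison of patient-level averages with common standard deviation SD.
- Standard error = SD × √(2/36) = 0.2357 SD.
- 95% half-width = 1.994 × 0.2357 = 0.470 SD (t quantile, 70 degrees of freedom).
- Difference detectable with 80% power = (1.994 + 0.847) × 0.2357 = 0.670 SD.
- Adjusting for baseline with correlation r multiplies both by √(1 − r²):

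| Assumed r | 95% half-width (SD) | Detectable at 80% power (SD) |
|---|---|---|
| 0 | 0.470 | 0.670 |
| 0.3 | 0.449 | 0.639 |
| 0.5 | 0.407 | 0.580 |
| 0.7 | 0.336 | 0.478 |

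**6. Multiplicity.** If oxygen, heart rate, systolic and diastolic pressure were each tested at 5%, the chance of at least one false positive would be 1 − 0.95⁴ = 18.5% if the tests were independent.

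**The case against.** The best reply is that the sentence loosely describes one thing: readings returning to baseline. It speaks of a single secondary endpoint, the Outcomes list has no separate item for change over time, and the Objectives frame the cardiovascular question as time to return. On that reading log-rank fits. This is possible, and it means the mismatch is not certain on every reading. But the parenthesis would then list a second item that adds nothing to the first, so the sentence still needs correcting, by deletion.

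A second reply is that a journal article condenses a fuller protocol, and that the analysis of serial secondary readings is commonly left there or to the analysis plan. That would answer a complaint of omission. Here the article does state a method, and the stated method does not fit.

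Three stronger readings are tempting and are not supported:
- A reader might infer a longitudinal heart rate and blood pressure endpoint from Adverse events, which mentions "the measurements of blood pressure and heart rate variations, which are the objectives of the present protocol". That is a passing cross-reference in a safety paragraph. It does not define an endpoint, and the Objectives speak of time to return.
- A reader might infer that log-rank is blind to any difference in size. It is not: a larger change that also takes longer to clear will lengthen return times and can be detected.
- A reader might want to put a figure on the lost power. The reading interval, the spread and the link between size and duration of change are not given. The heart-rate rises reported in the Background come from other intraosseous systems and are not a contrast between the two arms of this trial.

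**Conclusion.** The point holds as a minor one. The article assigns Kaplan-Meier and log-rank to change in measurements over time, and that method cannot compare serial readings. Either the method or the endpoint wording has to change.

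The conclusion rests on reading the cross-reference as pointing to the only between-arm method given for heart rate and blood pressure, and on taking change over time as a separate item because it is listed as one. It does not depend on which measurements are meant, which the article leaves unclear. The size of any loss of power cannot be stated. The primary analysis and the sample size are unaffected.

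**What to change.** If only return time is meant, delete the words on change over time. Otherwise replace the sentence along these lines:

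- Time to baseline O2 is compared by Kaplan-Meier and log-rank.
- Change over time is compared on the readings from T+4 to T+14 of oxygen saturation, and of heart rate and blood pressure only if the sponsor means to include them. The comparison uses a repeated-measures model with arm, time and arm-by-time terms, adjusted for the T0 to T+4 baseline. The between-arm difference is reported with its 95% interval at the 5% secondary level.
- For oxygen, which is capped at 100%, a Wilcoxon test compares each patient's maximum fall from baseline.
- These results are labelled supportive.

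The covariance structure should be left to the trial statistician, since the reading interval is not given. A difference averaged over the whole window would mix size with duration and dilute a brief peak. The arm-by-time term and, for oxygen, the maximum fall help with this.

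The cost is a few sentences and a little more secondary analysis on readings already collected, with no new patients, visits or measurements. The downside is added multiplicity if several parameters are tested, including at 5% the heart rate and blood pressure measurements whose primary tests are held to 1.7%. The supportive label is there for that reason.
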